#### Examining functional connectivity network changes from the Structure Learning training

Functional brain networks will be extracted through spatial group independent component analysis (GICA) in CONN [66]. Preprocessed EPI data from Training and Control groups in both sessions, i.e. Pre-test and Post-test, will be included in the GICA. We will first use principal component analysis to reduce dimensionality at both participant and group levels. Participant-specific spatial maps for each component will then be subjected to GICA3 back reconstruction to estimate spatial independent neural patterns for identification of functional brain networks [66]. We will then compute intrinsic and extrinsic connectivity to examine changes in functional connectivity, i.e. post-test minus pre-test and its relation to the Structure Learning training measures. Intrinsic connectivity is computed based on the correlation between filtered time course of each voxel with every other voxel in the participant-specific component. Extrinsic connectivity is computed based on the correlations of time series between cortical ICA components with striatal regions defined using the Melbourne Subcortex Atlas (https://www.nitrc.org/projects/msa) [67]. All correlation matrixes will be standardised with Fisher *z*-transformation and averaged to derive a mean index of functional network connectivity for each participant and session. These are then correlated with behavioural index of Structure Learning performance, such as strategy index with the Robust correlation toolbox [68].

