**Methods:**

Participants are pseudo-randomised to either the Training or Control group, while matched on age, sex, intelligence and cognitive flexibility performance. In the Training group, participants undergo around 2 weeks of training (at least 13 sessions) on Structure Learning. In the Control group, participants do not have to undergo any training and are never exposed to the Structure Learning task. The effects of Structure Learning training are investigated at both the behavioural and neural level. We measured covariates that can influence an individual’s training performance before the training phase and outcome measures that can potentially show training benefits after the training phase. At the behavioural level, we investigated outcomes in both cognitive and social aspects with a primary focus on executive functions. At the neural level, we employed a multimodality approach and investigated potential changes to functional connectivity patterns, neurometabolite concentration in the frontal brain regions, and brain microstructure and myelination.

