**Discussion:**

We reported the development of a novel training programme based on Structure Learning that aims to hone a general learning ability to potentially achieve extensive transfer benefits across various cognitive constructs. Potential transfer benefits can be exhibited through better performance in outcome measures between Training and Control participants, and positive associations between training performance and outcomes after the training in Training participants. Moreover, we attempt to substantiate behavioural findings with evidence of neural changes across different imaging modalities by the Structure Learning training.

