On a neural level, we employ a multimodality approach to examine potential neural benefits brought about by the cognitive training with both functional, i.e. resting-state functional magnetic resonance imaging (rs-fMRI) and magnetic resonance spectroscopy (MRS), and structural brain scans, i.e. multi-parameter mapping (MPM). Studies adopting training protocol based on Structure Learning have showed promising preliminary results of the potential neural benefits and demonstrated that the functional connectivity of the frontal-striatal circuits could predict decision performance [33, 34]. Building on findings from previous research, we hypothesise that we will see significant correlations of performance in the Structure Learning training programme with the frontal-cortico-striatal functional connectivity. Functional connectivity measures derived from rs-fMRI allow us to investigate functional networks within the brain but not discriminate between inhibitory and excitatory mechanisms. However, cognitive flexibility changes have been associated with neurometabolite changes in the prefrontal networks controlled by glutamatergic (excitatory) pyramidal neurons and GABAergic (inhibitory) interneurons [35–37]. Furthermore, GABAergic inhibition was found to optimise perceptual learning and decision making [38, 39]. Hence, the inclusion of MRS measurement of the neurotransmitter, γ-aminobutyric acid (GABA), will complement our findings in rs-fMRI and we hypothesise that higher GABA measured in the prefrontal cortex, an indication of better suppression of irrelevant information, will correlate with better Structure Learning performance. Previously thought to be a structurally permanent feature, recent evidence suggests that the rate and pattern of myelinisation in white matter can be modulated by learning and adaptation to novel experiences (for a review [40]). These changes, otherwise known as myelin plasticity, can play a pivotal role during learning, as well as after learning for consolidation. The present study will use MPM-R1 and R2* to probe myelinisation distribution as a measure of the speed of information processing [41] in response to environmental changes. Here, we hypothesise that MPM measures that reflect the extent of myelinisation in frontal-striatal regions, particularly within the cortex, will be associated with one’s performance during the Structure Learning training.

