### Outcomes {12}

In the present study, multiple behavioural tasks are administered to measure various cognitive constructs. Primary behavioural constructs under investigation include Structure Learning, cognitive flexibility, inhibition, and working memory. Secondary behavioural constructs under investigation include creativity, intelligence, problem-solving, language skills, numeracy skills, social tendencies, and decision making. These measures are conducted only at pre-test assessment, i.e. baseline, only at post-test assessment, i.e. after the end of structure learning training and approximately 2 months from pre-test assessment, or at both pre-test and post-test assessments. Specifically, we administered secondary behavioural constructs measuring language skills, numeracy skills, and intelligence (with the exception of the Raven’s Advanced Progressive Matrices) only at pre-test assessments as they are traits that remain relatively stable across the adult lifespan. We administered primary and secondary behavioural constructs measuring cognitive flexibility (with the exception of the Colour Shape Task), inhibition, working memory, creativity, and problem-solving only at post-test assessments to eliminate possibility of practice effects. Finally, matching tasks, i.e. Colour Shape Task and Raven’s Advanced Progressive Matrices, secondary behavioural constructs that measure social tendencies and decision making (and hence more impervious to practice effects) and all secondary neuroimaging constructs are measured at both pre and post-test assessments. Both the Control and Training groups undergo the same measures at pre and post-test assessments. However, measures for Structure Learning are collected only for the Training group. In addition, we investigate potential neural benefits of the Structure Learning training by assessing secondary neuroimaging outcomes both structurally and functionally. Detailed information regarding the individual tasks used this study can be found in Appendix B in the supplementary information.

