#### Secondary neuroimaging outcomes

All structural and functional scans are acquired on a 3 T Siemens MAGNETOM Prisma MRI scanner (Siemens Medical Systems, Erlangen, Germany) with a 64-channel head coil. MRI scans were conducted at two timepoints, namely pre-test and post-test for all participants. The same scan sequence is used for all pre-test and post-test MRI scans within each participant. However, there can be changes in scan sequence between participants due to technical issues.(1) Resting-state functional MRI datars-fMRI can reveal functional connectivity within and across brain networks that subserve task performance. A 10-min run of rs-fMRI data is acquired at both pre-test and post-test to investigate functional brain network changes that may result from the Structure Learning training. Before the rs-fMRI scan, participants are instructed to relax, fixate at a white cross presented at the centre of the screen, and to let their mind wander and not think about anything in particular. rs-fMRI images are acquired using Gradient Echo type Echo Planar Imaging (GRE-EPI) sequence with the following parameters: repetition time (TR) = 1280 ms; echo time (TE) = 30 ms; flip angle = 74^◦^; resolution matrix = 220 × 110 × 64; field of view (FOV) = 220 mm; thickness = 2.0 mm; acquisition voxel size = 2 × 2 × 2 mm^3^ resolution; integrated Parallel Acquisition Techniques = 4. A total of 64 slices are used to cover the whole brain including the cerebellum. Each 10-min run results in 462 volumes. In addition, high-resolution T1-weighted structure images are acquired using a Magnetisation Prepared Rapid Acquisition Gradient echo (MPRAGE) sequence with the following parameters: TR = 2000 ms; TE = 2.26 ms; inversion time = 800 ms; flip angle = 8°; FOV = 256 × 256; slices = 176; thickness = 1.0 mm; voxel size = 1 × 1 × 1 mm^3^).(2) Multi-parameter mappingMPM allows us to investigate different aspects of microstructural changes in grey matter and white matter. Recent evidence suggests that myelination is associated with behavioural plasticity in learning [41]. Hence, we focus on MPM parameters sensitive to myelin content, such as R1 and MT. All MPM scans are acquired with a 64-channel radio-frequency (RF) receive head coil and RF body coil for transmission. We use a multi-centre validated MPM protocol [48] in the present study. Three different multi-echo FLASH scans will be acquired with predominant T1-, PD-, and MT-weighting with appropriate choice of the TR and the flip angle. Multiple gradient echoes are acquired with alternating readout polarity at eight equidistant TE between 2.46 and 19.68 ms for the T1w, MTw, and PDw acquisitions. Acquisition parameters for T1-weighting and PD-weighting are as follows: voxel size = 1 × 1 × 1 mm^3^; slices = 176; FOV = 256; resolution matrix = 256 × 256; parallel imaging using GRAPPA factor in the phase-encoding (PE) direction = 2; 6/8 partial Fourier in partition direction, non-selective RF excitation, readout bandwidth BW = 480 Hz/pixel, RF spoiling phase increment = 50°. MT-weighting is achieved by applying an off-resonance Gaussian-shaped RF pulse (4 ms duration, 220° nominal flip angle, 2 k Hz frequency off set from water resonance) prior to the excitation. A pair of RF sensitivity maps are collected before each FLASH scans with the following parameters: 4 mm isotropic resolution, matrix = 256 × 64 × 48, parallel imaging using GRAPPA factor 2 in phase-encoding direction. The total acquisition time is around 15 min. The data-driven approach, i.e. unified segmentation-based correction of R1 maps for RF transmit inhomogeneities (UNICORT), is used to estimate B1 transmit bias field map [49].(3) Magnetic resonance spectroscopyMRS allows for non-invasive in vivo quantification of brain neurometabolites. In the present experiment, we targeted the measurement of the inhibitory neurotransmitter, GABA, in bilateral dorsolateral prefrontal cortex (DLPFC). Prior to all MRS scans, a high-resolution T1-weighted structural scan along the sagittal plane (MPRAGE; TR = 2000 ms; TE = 22.6 ms; TI = 800 ms; flip angle = 8°; FOV = 256 × 256; slices = 176; voxel size = 1 × 1 × 1 mm^3^) is acquired. We then 3D-reconstruct the axial and coronal planes and use images from all three planes to guide our voxel positioning on the DLPFC. We try to achieve consistent MRS voxel placement between subjects and sessions with the use of salient anatomical landmarks such as the dorsal anterior cingulate cortex, superior frontal gyrus, and middle frontal gyrus. In addition, we also try to maximise the sampling of grey matter in each region during voxel placement. After voxel placement, we ensure a homogeneous B_0_magnetic field within the DLPFC voxel with a two-step process. An automated B0 map-based shimming is first used to correct for shifts in linear gradients in the field. Subsequently, an interactive manual shimming procedure is used to correct for residual high-order heterogeneities in the B0 magnetic field. We aim to obtain an eventual shim that is as close to 16 Hz or preferably less than 16 Hz (full-width at half-maximum; FWHM) spectral linewidth. We then measured GABA levels with the widely used technique known as Mescher-Garwood Point Resolved Spectroscopy (MEGA-PRESS) [50, 51]. MEGA-PRESS implements J-difference editing to derive an edited signal that we then use it to quantify GABA levels. Two single voxel edited MR spectra are acquired from a 30 × 15 × 30 mm^3^ (in the *x*, *y*, and *z* dimensions) voxel of interest positioned separately in the left and right DLPFC. Two interleaved datasets are acquired within a single acquisition namely: (1) an edited ‘On’ inversion pulse at 1.98 ppm and (2) an ‘Off’ inversion pulse elsewhere at 7.5 ppm. Additional MEGA-PRESS parameters used are as follows: TR = 2000 ms; TE = 68 ms; spectral bandwidth = 1850 Hz; data points = 2048; readout duration = 1107 ms. We also acquire unsuppressed water spectra as a separate scan to allow for concentration reference to the water tissue. In total, 128 spectral averages (128 ‘On’ and 128 ‘Off’ pulses) are acquired during the metabolite scan and 4 spectral averages are acquired during the water scan resulting in a total scan duration of around 9 min.

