#### Examining changes in myelinisation distributions in frontal-striatal regions from the Structure Learning training

Parameter maps will be generated based on Weiskopf et al [48]. After normalisation and smoothing, we will extract mean MPM measures from masks of ICA components derived from the rs-fMRI GICA analysis. Difference scores from MPM parameter maps will be correlated with behavioural indexes computed from Structure Learning training to investigate the relationship between myelinisation distributions with how one performed during the Structure Learning training. We are expecting significant correlations to manifest in cortical regions. 

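### The planned neural tests are Training-only associations, so without a Training-versus-Control contrast they cannot support neural change caused by training

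*Protocol article*

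**What the plan says.** All quotations are from the protocol article.

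- **Aim.** The abstract's Discussion looks for "evidence of neural changes across different imaging modalities by the Structure Learning training". Objectives {7}, the rs-fMRI text under Secondary neuroimaging outcomes, and the three neural headings under {20a} likewise present neural change as a result of the training.
- **Hypotheses.** Those in Objectives {7} are correlational: connectivity, GABA and myelin-sensitive MPM measures are each expected to relate to Structure Learning performance. The GABA hypothesis concerns a level, "higher GABA measured in the prefrontal cortex".
- **Tests.** For connectivity, the post-minus-pre indices are computed and "These are then correlated with behavioural index of Structure Learning performance, such as strategy index with the Robust correlation toolbox". GABA+ change is handled in the same way. For MPM, "Difference scores from MPM parameter maps will be correlated with behavioural indexes computed from Structure Learning training".
- **Who has the indices.** Outcomes {12}: "measures for Structure Learning are collected only for the Training group". The abstract says that in the Control group "participants do not have to undergo any training and are never exposed to the Structure Learning task".
- **Who is scanned.** Secondary neuroimaging outcomes: "MRI scans were conducted at two timepoints, namely pre-test and post-test for all participants".
- **Use of Control scans.** They enter the group independent component analysis, whose component masks also serve MPM. No other use is stated.
- **Group comparison.** The only stated Training-versus-Control comparison is on post-test executive function measures (Evaluation of efficacy of Structure Learning training).

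**The concern.** A correlation between change and performance inside the trained arm does not estimate the mean change due to training, and it can be non-zero when training does nothing. People who learn the task well may differ beforehand in ability or in baseline neural level, and either can carry through into the change score. Only the randomised comparison with Controls separates training from time, rescanning and such prior differences. The trial collects the data for that comparison, but the plan as written does not name it.

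At stake is the interpretation of the secondary neural aim. If the correlations are the only neural results, statements about change from training would rest on an analysis that contains no untrained participants.

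There is also a smaller mismatch for GABA: the hypothesis concerns the level, but the planned test uses only the change.

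**Working it through.** **1. Can Controls enter the named tests?** Each {20a} neural test needs a Structure Learning index. Outcomes {12} gives that index to the Training group only, so Controls cannot enter. The strategy-subgroup analysis classifies Training participants only. Connectome-based predictive modelling is exploratory and its sample is not stated. None of these is a Training-versus-Control contrast.

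**2. The plan's own rs-fMRI figure.** Inputs from Sample size {14}: r = 0.46 and 35 per group. Alpha 0.05 and power 0.8 are taken from the behavioural calculation there; two-sided testing is assumed.

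n = ((1.960 + 0.842) / atanh(0.46))² + 3 = 34.7, rounded up to 35.

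The figure reproduces as a single-sample correlation, so a second group of 35 adds nothing to that test. At n = 50 the detectable correlation is tanh(2.80 / √47) = 0.39.

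**3. Can the correlation arise without a training effect?** Illustration, with these assumptions:

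- performance correlates r with the pre-test neural value;
- pre and post values have equal variance and correlation ρ;
- performance relates to the post value only through the pre value.

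The covariance of performance with change is then rρ − r, and the SD of change is √(2(1 − ρ)). Hence corr(change, performance) = −r√((1 − ρ)/2). Take r = 0.46 (the protocol's planning value, placed here on the baseline by assumption) and n = 50. The chance of p < 0.05 comes from Fisher's z:

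| Assumed ρ | Correlation with change | Chance of p < 0.05 |
|---|---|---|
| 0.3 | −0.27 | 48% |
| 0.6 | −0.21 | 30% |
| 0.8 | −0.15 | 17% |

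With no relation to baseline, the chance would be 5%.

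**4. What would the missing contrast deliver?** Two-group comparison, two-sided alpha 0.05, noncentral t, with d in SD units of the quantity compared. The protocol gives no between-group effect for neural change, so the d values below are assumptions (0.25 is the value of its behavioural calculation).

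| Usable per group | d detectable at 80% power | Power at d = 0.2 | Power at d = 0.25 | Power at d = 0.5 |
|---|---|---|---|---|
| 35 | 0.68 | 13% | 18% | 54% |
| 48 | 0.58 | 16% | 23% | 68% |
| 50 | 0.57 | 17% | 24% | 70% |

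The 48 is what 60 per group leaves after 20% attrition (60 × 0.8). Adjusting the post value for the pre value multiplies the detectable difference, in SDs of the post value, by √(1 − ρ²). At 50 per group this gives 0.54, 0.45 and 0.34 for assumed ρ of 0.3, 0.6 and 0.8.

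**The case against.** The strongest reply is that the tests match the hypotheses. Objectives {7} predicts correlations, and the MPM analysis text says it examines how myelin measures relate to training performance. That stands, and it is a reason to keep the correlations. The gap is between them and the wider aim and headings.

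A group contrast may also be intended. The choice of comparators {6b} gives protection of the imaging results as a reason for a passive control, GABA is sized per group, and the connectivity text speaks of examining changes as well as their relation to training. A full analysis plan might therefore contain one. But {20a} names a specific test for each modality, and none uses the Controls.

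Stronger readings are tempting, but the documents do not support them:

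- **That every neural analysis is a correlation.** The additional analyses compare strategy subgroups and plan predictive modelling.
- **That the trial cannot estimate the group contrast.** Both groups are scanned twice, so it can.
- **That scanner drift explains a correlation.** Drift common to all participants shifts the mean change and creates no correlation.
- **That varying scan sequences undermine the tests.** The article does say "there can be changes in scan sequence between participants due to technical issues", but it also keeps the sequence the same for both scans of one participant. Additive sequence effects therefore cancel in the change score.
- **That the behavioural evidence has the same defect.** The abstract lists within-Training associations beside the group difference, {20a} makes the group difference primary, and the model linking training to flexibility includes baseline covariates.

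Finally, the added contrast has low power for small effects. That is true, and it limits what the contrast can show. It does not make the correlations a substitute.

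**Conclusion.** The point holds in a limited form. The neural tests named under {20a}, and the strategy-subgroup analysis, use Training participants only, and no Training-versus-Control neural contrast is stated. They can address the correlational hypotheses in Objectives {7} but not neural change caused by training.

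The 30% figure, with a range of 17% to 48%, illustrates how a correlation can arise without a training effect. It rests on the assumed baseline correlation of 0.46 and the assumed pre/post correlations, and it is not an estimate for this trial. The missing contrast would detect about d = 0.57 at 50 per group unadjusted, with 17% power at an assumed d = 0.2, so it gives an estimate at pilot level.

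This should be fixed. It is not critical to the trial, because the neural outcomes are secondary, the aim is described as pilot-level, and the primary behavioural comparison does not depend on them.

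**What to change.** - For each pre-specified neural measure, add a Training-versus-Control comparison of the post-test value adjusted for the pre-test value, in all participants with usable scans. Report it with a confidence interval, and name it as the test of neural change from training. A scan-sequence term is optional.
- Keep the Training-only correlations for the hypotheses in Objectives {7}, and describe them as associations in the headings and in the reporting.
- For GABA, also correlate the GABA+ level with Structure Learning performance, and state at which time point the level is taken, since the hypothesis does not say.

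The cost is some analysis-plan wording and a few extra models on scans that the protocol already schedules. Conclusions about neural effects become more modest, and the intervals for the group contrast will be wide.

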#### *Examining bilateral dorsolateral prefrontal (DLPFC) GABA* + *concentration changes from the Structure Learning training*

The basis set of brain model metabolite spectra from LCModel (version 6.3) will be used to fit preprocessed MRS data to derive GABA + concentration from the right and left DLPFC. We will model creatine(tCre), choline(tCho), glutamate, Glx(Glu + glutamine), and NAA from the edit-off spectrum, and GABA + from the difference spectrum. Resultant model fits for the MRS data will be assessed for quality based on Cramer-Rao Lower Bound (CRLB) values of less than 20% for bilateral DLFPC and sessions and signal-to-noise ratios of > 20. GABA + concentration differs between tissue types. We will employ a tissue correction strategy to correct for the dependency of GABA + on voxel tissue composition. The percentage of grey matter (GM), white matter (WM), and cerebrospinal fluid (CSF) in each of the measured voxel during MRS will be computed and GABA + concentration will be divided by GM/(GM + WM + CSF). Similar to the planned analysis for rs-fMRI, we will then correlate the changes in corrected GABA + concentration, i.e. post-test minus pre-test with behavioural index from the Structure Learning training with the Robust correlation toolbox [68].

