### Methods in analysis to handle protocol non-adherence and any statistical methods to handle missing data {20c}

Any deviations from the protocol due to human or technical errors are noted down in an Excel sheet and corrected whenever possible. Missing data in behavioural outcomes are accommodated with the use of mixed effects models. Data imputation will be performed only if we have more than 20% of data missing for any one of the behavioural measures. We will not perform any data imputation for neuroimaging data. Instead, any unusable data in a particular MRI modality will be discarded and neuroimaging data from other intact MRI modalities kept for analyses. Hence, the eventual number of participants used for analyses in the different neuroimaging modalities may differ. Finally, all data from any participants who have withdrawn from the study will be excluded from the data analyses.

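### The 20% limit on percentage CRLB has the GABA+ estimate in its denominator, so it preferentially discards low-GABA+ spectra; the size is unknown and the effect on the planned change-score correlation is mild

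*Protocol article*

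**What the plan says.** In the protocol article, Statistical methods {20a}, the subsection on DLPFC GABA+ changes assesses the model fits by "Cramer-Rao Lower Bound (CRLB) values of less than 20% for bilateral DLFPC and sessions and signal-to-noise ratios of > 20". There are four spectra per participant: left and right DLPFC, before and after training.

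The section on non-adherence and missing data {20c} supplies the consequence: "any unusable data in a particular MRI modality will be discarded and neuroimaging data from other intact MRI modalities kept for analyses". It adds: "We will not perform any data imputation for neuroimaging data".

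The planned GABA+ analysis is to "correlate the changes in corrected GABA + concentration, i.e. post-test minus pre-test with behavioural index from the Structure Learning training". The hypothesis in Objectives {7} is worded on level rather than change: "higher GABA measured in the prefrontal cortex, an indication of better suppression of irrelevant information, will correlate with better Structure Learning performance".

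Secondary neuroimaging outcomes gives a linewidth target at acquisition: "We aim to obtain an eventual shim that is as close to 16 Hz or preferably less than 16 Hz". The article does not carry this target into the exclusion criteria.

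**The concern.** A quality limit should remove poor spectra regardless of what they show. A percentage CRLB cannot do that, because it divides the fitting-error bound by the estimated concentration. Two spectra of identical quality get different percentages if one person has less GABA+, and the lower one is more likely to fail. The rule therefore selects on the quantity being studied.

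Three things are at stake:
- The retained GABA+ levels are shifted upward and their range is narrowed.
- Participants are lost for a reason unrelated to scan quality.
- If training shifts GABA+ in one group, the chance of exclusion differs between groups.

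The article states no guard against this, such as an absolute limit or an analysis without the rule.

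**Working it through.** The 20% limit is a threshold, not a calculated figure, so there is nothing of the plan's own to reproduce first.

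**Inputs from the article.** CRLB limit of 20%; two sides and two sessions; SD of 0.24 for GABA peak height relative to water (Sample size {14}); discard without imputation ({20c}).

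**Assumptions not in the article.** Mean GABA+ of 1, so that SD 0.24 is a coefficient of variation of 24%, with SD 0.15 as the lower alternative; typical CRLB of 10%, 12% or 15%; equal absolute noise in all spectra; correlation 0.5 among the four values; a participant is lost if any of the four spectra fails.

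**Step 1: direction.** CRLB% = 100 × s / C, with s the error bound and C the estimated GABA+. The condition CRLB% < 20 is the same as C > 5s. If the typical CRLB at C = 1 is t%, then s = t/100 and a spectrum fails when C < t/20:
- t = 10%: fails below 0.50
- t = 12%: fails below 0.60
- t = 15%: fails below 0.75

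**Step 2: one spectrum.** P(fail) = Φ((t/20 − 1)/SD). For SD 0.24 the arguments are −0.50/0.24 = −2.08, −0.40/0.24 = −1.67 and −0.25/0.24 = −1.04, giving about 2%, 5% and 15%.

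**Step 3: four spectra, effect on level** (simulation of 400,000 people, no mean change).

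| SD | Typical CRLB | Lost, all four must pass | Lost, each side judged alone | Retained mean (true 1) | SD of person mean (before → after) |
|---|---|---|---|---|---|
| 0.24 | 10% | 6% | 3.4% | 1.02 | 0.19 → 0.17 |
| 0.24 | 12% | 14% | 8.4% | 1.04 | 0.19 → 0.16 |
| 0.24 | 15% | 36% | 24.1% | 1.10 | 0.19 → 0.14 |
| 0.15 | 10% | 0.2% | 0.1% | 1.00 | 0.12 → 0.12 |
| 0.15 | 12% | 1.4% | 0.7% | 1.00 | 0.12 → 0.12 |
| 0.15 | 15% | 14% | 8.5% | 1.03 | 0.12 → 0.10 |

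**Step 4: the planned change score.** At SD 0.24, the SD of the retained post-minus-pre change is k = 0.98, 0.96 and 0.91 of the full SD for typical CRLB of 10%, 12% and 15%. With a true correlation r = 0.40, range restriction gives r′ = k·r / √(1 − r² + k²·r²). At k = 0.91 this is 0.364 / √(0.84 + 0.1325) = 0.37; at k = 0.98 and 0.96 it is 0.39. The simulated values agree. With SD 0.15 and typical CRLB 15% the result is about 0.385.

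**Step 5: falls against rises.** With no true mean change, the retained change has mean 0.000 and no material skew: a low pre-test value that rises is lost as often as a low post-test value that results from a fall. With a true shift of 10% of the mean the losses differ:

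| SD | Typical CRLB | Lost if GABA+ falls 10% | Lost if GABA+ rises 10% | Retained mean change (true −0.100) |
|---|---|---|---|---|
| 0.24 | 12% | 21% | 10% | −0.089 |
| 0.24 | 15% | 47% | 29% | −0.081 |
| 0.15 | 15% | 28% | 9% | −0.087 |

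**Step 6: noise allowed to vary.** A separate simulation used correlation 0.6, estimation noise, and constant or variable noise (16 scenarios, typical CRLB 8% to 15%). Those excluded had lower mean true GABA+ than those kept in every scenario. With variable noise the gap was smaller, because some noisy spectra with ordinary GABA+ also failed. At SD 0.24 and CRLB 12%, the means kept and excluded were 1.06 and 0.75 with constant noise, and 1.07 and 0.82 with variable noise.

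**The case against.** The strongest reply is that the planned analysis uses change, not level. A bias common to both sessions cancels in a difference, and Step 4 shows little harm to the correlation. This stands. The level bias bears on the hypothesis in Objectives {7}, but the analysis section specifies no test of level.

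A reader might infer that the rule generally deletes falls and keeps rises. It does not: both sessions must pass, so without a mean shift the loss is symmetric. The asymmetry needs a true shift, which the article neither states nor assumes.

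A reader might also infer that one failing spectrum certainly removes the participant. The article says only that fits are assessed for quality. Discarding comes from {20c}, and neither section says whether one failed voxel drops the whole participant. Requiring all four is the natural reading of the sentence, but not a settled one.

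The numbers rest on outside assumptions. The SD of 0.24 is for peak height relative to water, not fitted GABA+ concentration, and its mean is not given. Equal noise makes every exclusion a low-GABA+ exclusion by construction, whereas real failures will include poor spectra. A negligible effect is within the range. The SNR criterion is a second gate which, taken on a reference peak, does not depend on GABA+.

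These points limit the size. They do not alter the direction, which follows from the definition of the percentage.

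**Conclusion.** The concern holds in a limited form. At equal noise, a percentage-CRLB limit of 20% preferentially removes low-GABA+ spectra, and the article states no safeguard. The share of participants lost runs from 0.2% to 36% under the stated assumptions and cannot be narrowed from the documents. At the upper end it would by itself exceed the 20% attrition allowance in Sample size {14}.

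GABA+ level is biased upward, by at most about 10% in these scenarios. The planned change-score correlation is weakened only slightly. Unequal loss of falls and rises, and hence exclusion that differs by group, arises only if training truly shifts mean GABA+. Since this is a secondary imaging outcome and the repair is cheap, it is a worthwhile improvement rather than a serious fault.

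**What to change.** In the DLPFC GABA+ subsection of {20a}:

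- Base exclusion on criteria that do not contain the GABA+ estimate: SNR > 20 measured on a named reference peak such as NAA or creatine, linewidth against the 16 Hz target, and visible artefact. Alternatively, set the limit on the absolute CRLB (percentage × estimate).
- Say that the rule applies per voxel side, so that a failed left voxel does not remove the right. At SD 0.24 this cuts the losses from 6%, 14% and 36% to 3.4%, 8.4% and 24.1%, even under the present limit.
- Report results under the 20% percentage rule as a sensitivity analysis.

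This changes wording only. Linewidth, SNR and CRLB come from the acquisition and fits already planned, and no new scans are needed. The downside is that some noisier low-GABA+ estimates stay in; they can be down-weighted by their absolute error.
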